#### Preliminary considerations

There are no trials of preventive interventions similar to ours on which we could base hypotheses about the likely size of the effect of our intervention. A meta-analysis comparing the effect of psychotherapy relative to waitlist control estimated an average standardised effect of Hedges’ *g* = 0.75 [97, 98]. Given that our intervention targets an at-risk population, rather than a clinical one, we assumed that the minimum standardised effect size we wished to detect was about half Munder et al.’s [97] estimate. We thus used a standardised effect size of δ = 0.4 for the power analysis calculations, in conjunction with considerations about clinically meaningful effect sizes.

Psychopathology will be assessed using the SDQ Total Difficulties Score. There is no consensus regarding how many point difference on the SDQ constitutes clinically meaningful change [99]. We considered that a post-intervention difference between 1 and 2 points between the intervention and control groups would be clinically meaningful. A 1-point difference corresponds to one of 20 assessed symptoms improving by 1 point; a 2-point difference corresponds to one symptom improving by 2 points, or two symptoms by 1 point each. We estimated the standard deviation of the SDQ Total Difficulties Score using the data set from the Understanding Society study (*n* = 2100) that we also used to estimate our cut-off for eligibility (top 25% of SDQ scores). In the ‘eligible’ group (who had a score of 15 or higher, *n* = 604), the mean score was 19.1, with standard deviation 3.6. Raw effect sizes of 1, 1.5 and 2 points would correspond to standardised effect sizes of about 0.28, 0.42 and 0.56. We thus considered that, by powering for a standardised effect size of 0.4, we would be able to detect a 1.5-point difference in SDQ Total Difficulties Scores post-intervention.

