*Mental Wellbeing* will be assessed by the WEMWBS. There are few published data sets allowing estimation of the distribution of this scale among younger teenagers, and none for our specific at-risk population (top 25% in mental health problems). As the closest available approximation, we used data from the 2018 sweep of the Millennium Cohort Study (MCS), when cohort members were 17 years old. This was the only study we found that measured both SDQ and WEMWBS for the same participants. In contrast to our own study, the MCS used the short (7-item) version of the well-being scale, the SWEMWBS. Selecting the 25% participants with the highest SDQ total difficulties score (SDQ ≥ 15, *n* = 2473) gave us an estimate of SD = 4.7 for the SWEMWBS. We decided to assume the slightly larger SD = 5 for the calculations below, for simplicity and to err on the conservative side. It is not clear what size of points difference on the SWEMWBS is clinically meaningful or subjectively important to children, although change scores as small as either 1 or 3 points have been cited as minimally important change on the individual level [100]. Raw effect sizes of 1, 2 and 3 points would correspond to standardised effect sizes of about 0.2, 0.4 and 0.6. Since there is a high correlation between the 7-item SWEMWBS and the 14-item WEMWBS, we assume that these results will scale appropriately to the longer version of the scale, which we will use in our study.

The aim of the power analysis was to determine the number of schools that need to be recruited to give us 90% power to detect a moderate effect of the intervention (δ = 0.4) for each of the SDQ Total Difficulties Score and the WEMWBS. To correct for multiple testing of our two primary outcomes, we set alpha at 0.025 for a two-sided test. We will select larger than average schools such that each school year will have around 240 pupils or more. With 25% of pupils meeting the entry threshold, and estimating that 50% agree to take part, we considered that we are likely to recruit 30 students per school year, and thus 60 students per school. The group intervention was assumed to be delivered in groups of 10. Thus, we expect to run approximately three intervention groups per school.

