We decided on 1:1 randomisation between treatment and control participants. We assumed the within-group correlation to be ICC_group_ = 0.05 and the within-year correlation to be ICC_year_ = 0.02, which are both conservative: in similar trials, intraclass correlations are often smaller (smaller ICCs would result in higher power; [96]). We also assumed a within-student autocorrelation from baseline to post-intervention measures of *r*_participant_ = 0.5. This is again conservative: the median within-participant correlation in trials is estimated to be 0.59 [101] (a higher *r*_participant_ would result in higher power). Furthermore, we assumed that the outcomes would not be related to school, which is also conservative; within-school correlation would increase the power, as each school would act as its own control. Finally, our analysis assumed up to 20% of participants lost to follow-up in both the treatment and control groups.

Under these assumptions, 540 adolescents from nine schools will need to be recruited: 270 in the intervention arm, attending 27 treatment groups, and 270 in the control arm. This would give an estimated analysis sample (after loss to follow-up) of 432. The power to detect δ = 0.4 in one outcome at the 2.5% significance level is about 92.8%. There is some room in this design for unexpected recruitment difficulties, as the power would be 90.5% if only 25 treatment groups were run and 250 controls were recruited, which would happen, for example, if two schools were able to run only two intervention groups each, instead of three.

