### Statistical methods

#### Primary outcome analysis

The primary analyses aim to estimate the effect of the intervention on two primary outcomes: psychopathology and mental wellbeing. Psychopathology will be measured as the self-reported SDQ Total Difficulties score. The other primary outcome, mental wellbeing, will be assessed by the summary score on the Edinburgh Mental Wellbeing Scale.

The primary outcome analysis will use a partially clustered mixed effects model [102], which takes into account that participants are clustered in treatment groups in the intervention arm, but not in the control arm, via a random effect for treatment groups. The model will adjust for baseline score of the outcome measure. We will additionally control for clustering of all participants within school years via a fixed effect, and for clustering within schools via either fixed or random effects (details will be specified in the statistical analysis plan). The evidence for a treatment effect will be evaluated via a two-sided *t*-test on the coefficient of the treatment indicator variable (intervention versus control group) from the mixed effects model, using a 2.5% level of significance. Analyses will be carried out in the R software (R Core Team 2021). The primary endpoint will be post-intervention (see Fig. 4).

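### The stated 92.8% power takes no account of there being only 18 randomised school years; a cluster-level t reference gives about 88–90% ignoring school, or about 78–83% adjusting for school

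*Protocol article*

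**What the plan says.** Under Preliminary considerations, the protocol article sets out to "determine the number of schools that need to be recruited to give us 90% power" for each of two primary outcomes at a standardised effect of 0.4, and "we set alpha at 0.025 for a two-sided test". On correlation it says: "We assumed the within-group correlation to be ICC_group_ = 0.05 and the within-year correlation to be ICC_year_ = 0.02". It also assumes a baseline-to-post correlation of 0.5, no relation between outcome and school, and 20% loss in each arm.

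The result is nine schools, 27 treatment groups and 270 participants per arm, with 432 analysed. It concludes that "The power to detect δ = 0.4 in one outcome at the 2.5% significance level is about 92.8" per cent. It then says there is some slack, since "the power would be 90.5% if only 25 treatment groups were run and 250 controls were recruited".

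Trial design and Randomisation schedule make the school year the randomised unit, with one year group per arm in every school. Primary outcome analysis plans a two-sided t-test "on the coefficient of the treatment indicator variable (intervention versus control group) from the mixed effects model". That model has a random treatment-group effect and a fixed effect for school year; whether school is fixed or random is left to the statistical analysis plan. The power section gives neither a critical value nor degrees of freedom; it cites published formulae for partially clustered data.

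**The concern.** The calculation counts year-level variance in the standard error. That variance can only be estimated from the 18 randomised school years, or from nine within-school differences if school is in the model. With so few units the t critical value is well above 2.24, and power falls even though the standard error is unchanged. If the stated power carries no allowance for this, the 90% target may be missed on the plan's own assumptions. The reassurance about running only 25 groups would then rest on a margin that the base inputs do not supply.

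**Working it through.** **Inputs** (all from Preliminary considerations): effect 0.4; two-sided alpha 0.025; 27 groups of 8 analysed (216) and 216 controls; nine school years per arm; ICC_group 0.05; ICC_year 0.02; r = 0.5, so the variance factor is 1 − 0.25 = 0.75.

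**Variance of the standardised effect.** The text allows three readings.

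- A, correlations added to unit variance: 0.75 × [1/216 + 0.05/27 + 0.02/9 + 1/216 + 0.02/9] = 0.01167, SE 0.1080.
- B, components summing to 1: 0.75 × [(0.02/9 + 0.05/27 + 0.93/216) + (0.02/9 + 0.98/216)] = 0.01135, SE 0.1066.
- C, the 0.05 taken to include the year's 0.02: 0.75 × [(0.02/9 + 0.03/27 + 0.95/216) + (0.02/9 + 0.98/216)] = 0.01087, SE 0.1042.

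**Reproducing the stated 92.8%.**

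- Reading A, normal critical value 2.241: 0.4/0.1080 = 3.703, and Φ(3.703 − 2.241) = 92.8%. With t on 430 df it is 92.7%.
- Reading C, t on 36 df (27 groups + 9 control years): also 92.8%.
- Reading B with the normal value: 93.5%.

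**Reproducing the stated 90.5%** (25 groups, 200 analysed per arm, school years scaled to 25/3).

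- Reading A: 0.75 × [1/200 + 0.05/25 + 0.02/(25/3) + 1/200 + 0.02/(25/3)] = 0.0126, SE 0.1122. Power is 90.7% with the normal value and 90.5% with t on 398 df.
- Reading C with t on 25 + 25/3 = 33.3 df: 90.5%.

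So two routes reproduce both figures, and neither uses degrees of freedom from the randomised units.

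**Cluster-level reference.** Degrees of freedom are 18 − 2 = 16 if pairing is ignored (critical value 2.47), 9 − 1 = 8 with school adjusted for (2.75), and 7 with a year effect as well (2.84). Noncentral t power at 0.4, same standard errors:

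| Reading | 16 df | 8 df | 7 df |
|---|---|---|---|
| A | 87.8% | 80.5% | 78.1% |
| B | 88.7% | 81.6% | 79.2% |
| C | 90.1% | 83.4% | 81.1% |

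Simulation of school-year means under A and B agrees: 87.8–88.9% unpaired, 80.5–82.0% paired, and 77.5–79.1% paired with a year effect.

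**25 groups.** Across the three readings, with year clusters at 25/3 or kept at 9 per arm: about 85–88% on 16 df and about 75–81% on 7–8 df, against 90.5% stated.

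**Effect detectable with 90% power.** This is the SE times the noncentrality giving 90%: 3.83 (16 df), 4.22 (8 df) and 4.35 (7 df). Unpaired: 0.1042 × 3.83 = 0.40 to 0.1080 × 3.83 = 0.41 SD. School-adjusted: 0.1042 × 4.22 = 0.44 to 0.1080 × 4.35 = 0.47 SD; readings A and B alone give 0.45–0.47. At the article's SDQ standard deviation of 3.6, the school-adjusted range is 3.6 × 0.44 = 1.6 to 3.6 × 0.47 = 1.7 points, against the 1.5 points that the article says the trial can detect. The unpaired range stays within 1.5 points.

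**The case against.** The strongest reply has four parts.

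1. *The method is not shown.* This stands. A reader might infer that 92.8% can only come from a normal critical value. The documents do not support that: reading C with 33–36 df reproduces both figures to one decimal.

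2. *School adjustment is not fixed, and its benefit is ignored.* This stands in part. A reader might take 78–83% as the trial's actual power. That range needs school in the model, and fixed versus random is left to the analysis plan. It also charges the lost degrees of freedom while crediting no within-school correlation. If half of the 0.02 were shared within school (an assumption; reading B), power would be 87.6% on 8 df or 85.5% on 7 df.

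3. *The inputs are called conservative.* With r = 0.59, the median the article cites, reading B gives about 93% on 16 df and 87% on 8 df. If ICC_year were also 0.01 (an assumption), it gives 96% and 91.6%. So real slack may exist, and it would be too strong to say that none does. But the 92.8% and 90.5% are stated at the base inputs, and favourable alternatives do not make them right there.

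4. *The described model has no random school-year term, so its degrees of freedom are larger.* This does not rescue the figure. Simulated with the assumed year-level variance, that model rejects about 4–5.5% of the time under no effect, against a nominal 2.5%. Its apparent power is therefore not power at the stated alpha.

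**Conclusion.** The concern holds as a matter of reference distribution. It is not an arithmetic slip: the stated figures reproduce. At the plan's base inputs, no cluster-level reference gives 92.8%. Power is about 88–90% with pairing ignored, and about 78–83% with school adjusted for and no within-school correlation credited. The 25-group figures fall to about 85–88% and 75–81%, so 90.5% is not reached on either basis.

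A reader might conclude that the trial must miss its 90% target, or that 89% is a ceiling. Neither follows, since reading C with 16 df gives 90.1%. The result rests on the assumed year-level correlation of 0.02, equal cluster sizes, and testing against variation between randomised school years. The choice of degrees of freedom for the analysis may properly sit in the analysis plan; the point here is the power figure that the article itself states.

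**What to change.** Keep the sample size. In Preliminary considerations:

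- State the variance formula, how the group and year correlations combine, and the degrees of freedom behind the power.
- Restate power at 0.4 SD as a range on a cluster-level t reference: about 88–90% without school adjustment and about 78–83% with it, noting that within-school correlation would raise the latter. Alternatively, restate the effect detectable with 90% power: about 0.40–0.41 SD unpaired and about 0.44–0.47 SD school-adjusted.
- Withdraw the statement that 25 groups still give 90.5%, or requalify it with about 85–88% and 75–81%.

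No participants, schools or procedures change. The cost is a less favourable stated power.

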## Methods: data collection, management, and analysis

### Data collection methods

#### Data collection plan

To promote the data quality, all assessors are trained in measurement protocols and are provided with a manual outlining the procedure for collecting assessment data to enhance fidelity to the data collection protocol. Furthermore, all measures are delivered via a tablet, meaning participants do not report primary or secondary outcomes under observation, reducing the chances of biased responses. A log of any issues that occur during data collection will be recorded to monitor data quality throughout the duration of the project. All measures have previously been used with developmental samples and have demonstrated good reliability and validity in these samples.

#### Data management

Data from the cognitive-emotional training tasks will be collected via mobile applications designed to host the training tasks on tablets. Data from the emotion perception training task and emotion regulation training task will be collected via PsyTools, a software designed for hosting behavioural tasks and questionnaires. Data from the interoception task will be collected using a bespoke application that is uploaded to Firebase, a secure data storage server (https://firebase.google.com/docs/projects/learn-more?authuser=2&hl=en). Data from these tasks are stored on the host device and immediately uploaded to secure servers using encrypted transfer procedures. If there is no internet connection, data are encrypted and stored on the device until an internet connection has been established. No data from these tasks can be linked to individual participants from the servers nor the devices themselves. Anonymised data is transferred from the secure servers to UCL’s Data Safe Haven (https://www.ucl.ac.uk/isd/services/file-storage-sharing/data-safe-haven-dsh), a secure repository for storing, handling, and analysing data. Only the research team will have access to the data on UCL’s Data Safe Haven.

Data from the focus groups will be collected on an audio recording device that is only accessible to the research team. Audio recordings will then be uploaded to UCL’s Data Safe Haven for transcription. Once audio files have been transcribed, they will be securely destroyed.

### Data management

Data will be managed by an external company who provide data management services: Delosis. This company will be responsible for transferring data from the PsyTools app or extracting the data from the Firebase database. Our data management plan can be found in the Additional file 1: Appendix.

### Statistical methods

#### Primary outcome analysis

The primary analyses aim to estimate the effect of the intervention on two primary outcomes: psychopathology and mental wellbeing. Psychopathology will be measured as the self-reported SDQ Total Difficulties score. The other primary outcome, mental wellbeing, will be assessed by the summary score on the Edinburgh Mental Wellbeing Scale.

The primary outcome analysis will use a partially clustered mixed effects model [102], which takes into account that participants are clustered in treatment groups in the intervention arm, but not in the control arm, via a random effect for treatment groups. The model will adjust for baseline score of the outcome measure. We will additionally control for clustering of all participants within school years via a fixed effect, and for clustering within schools via either fixed or random effects (details will be specified in the statistical analysis plan). The evidence for a treatment effect will be evaluated via a two-sided *t*-test on the coefficient of the treatment indicator variable (intervention versus control group) from the mixed effects model, using a 2.5% level of significance. Analyses will be carried out in the R software (R Core Team 2021). The primary endpoint will be post-intervention (see Fig. 4).

#### Secondary analyses

Analogous partially clustered models will be estimated for.Each primary outcome at 1-year follow-upEach secondary outcome at both end of intervention and 1-year follow-up

#### Further analyses

Using structural equation modelling techniques, we will examine mediation of treatment effects using bootstrapped estimates of the indirect effect between treatment, mediator and outcome, as illustrated in Fig. 6 below. The mediation models will respect the clustered data structure and control for baseline outcome scores. A full analysis plan will be pre-registered on the Open Science Framework prior to the start of the analysis (see: https://osf.io/34jur/).

**Fig. 6 Fig6:**
[figure not shown]
Plot illustrating the proposed SEM examining the indirect effects of treatment and mediators on outcomes. Note, the measurement model for the latent factors here show to items per factor (x, y and u, v), but in our final model there will be more items per factor. Clustering in treatment groups is not represented in this diagram, but will be accounted for in the modelling

### Consent and assent procedures

All consent forms utilised in the current study will be sent to parents and adolescents by staff members at the participating schools. Consent forms will be provided in electronic or paper format, depending on the school’s typical procedure for acquiring parental consent. Electronic consent forms will be stored in secure servers provided by REDCap (https://projectredcap.org/) and physical copies will be stored in a secure filing cabinet only accessible to the study team.

### Data monitoring

Data security will undergo regular reviews by the research team to ensure it is compliant with our data management plan (see Additional file 1: Appendix). This data management plan will be reviewed annually to ensure no new risks are identified. The data will additionally be monitored by the data management provider.

### Ethics and risk management

All procedures involved in the study have been approved by UCL’s ethics committee (project number: 21815/001). We have designed the study materials to minimise the risk of harm to participants and have a strict safeguarding protocol in place. Those who wish to take part are provided with full, transparent information about the aims and content of the study to ensure that they can provide informed consent. Moreover, participants are reminded that they are free to withdraw from the study at any stage without providing an explanation. To ensure that there is no risk of harm to participants, we have utilised measures and task that have previously been used with this age group in previous research and are therefore appropriate for developmental populations.

We have also ensured that members of the research team are appropriately qualified to work with developmental populations. All members of the research team who work with adolescents or vulnerable adults will have a current Disclosure and Barring Service (DBS) certificate and will receive specific training about safeguarding. A risk-related triaging will be applied, such that urgent concerns are reported immediately to a clinically qualified member of the team (e.g. RL or PF), who can advise about the appropriate action and consult with the safeguarding lead at the Anne Freud Centre if necessary. Facilitators delivering the sessions will all be provided with bespoke training designed for the purposes of the course and delivered by the senior clinician on the team (RL). The training will be comprised of a minimum of 2 days of training with additional resources such as educational videos and a manual that facilitators can refer to. In addition, clinicians delivering the intervention are senior, experienced practitioners with expertise in the delivery of therapeutic interventions. These clinicians also have up to date training in identifying and referring high-risk participants, and any adolescents exhibiting symptoms of distress will be triaged according to the school’s policy regarding pupil wellbeing. Any adverse events or serious adverse events related to the trial will be stored confidentially by the study team and will be reported alongside the main trial outcomes. We define an adverse event as an incident that requires referral to a Child and Young Person Mental Health Support Team and/or GP (see Appendix III for a copy of the adverse event reporting form). 

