#### The ReSET group intervention

ReSET is a manualised intervention (including cognitive-emotional training elements) delivered in a group-based setting with up to 10 adolescents allocated to each group. Sessions will be held weekly over an 8-week period and each session lasts between 90 and 120 min. The sessions will focus on developing adolescents’ understanding of the links between their social relationships, emotions, and mental health. Here, we describe the structure of our intervention that integrates the cognitive-emotional training tasks with psychoeducation about communication and mental health.

The intervention will begin with young people having an individual meeting with the group facilitator to discuss the aims of the groups, their goals for taking part, and any questions they have about the sessions. These individual meetings will be used to identify where the young person may be experiencing interpersonal difficulties that can be addressed in the group sessions. Issues arising from interpersonal difficulties will be set as explicit goals by the young person (with the aid of the facilitator), which will allow the young people to self-monitor their progress throughout the duration of the intervention.

Each of the group sessions will begin with participants completing the Child Outcome Rating Scale (CORS), a clinical measure designed to monitor an individual’s progress during the therapeutic process [52, 53]. The CORS measures several domains of the young person’s life functioning, including their individual wellbeing, interpersonal wellbeing, social role, and overall wellbeing [53]. The CORS has been validated with adolescents aged 11–15 [52]. Clinical cut-offs will be used by facilitators to identify young people who may need additional support during the group, or those that may benefit from more targeted services. The CORS will also be utilised during the intervention sessions to consider links between the strategies discussed in the sessions, their impact on how participants communicate with those around them, and the relationships between social interactions and wellbeing. Drawing links between social interactions and wellbeing will be a core component of the psychoeducation content of the intervention, particularly in relation to communication.

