## Assignment of interventions

### Timing of randomisation

Randomisation will be performed at each school once that school has been provided with a list of participants scoring within the top 25% (i.e. above the cut-off score of 15) of the sample from both year groups. All eligible students will be invited to participate, and students will be randomised in each year group in a numerical order: (a) 1–10 (Group 1)—Term 1, (b) 11–20 (Group 2)—Term 2, and (c) 21–30 (Group 3)—Term 3. As our intervention runs over two academic years in some schools (April 2023–March 2024), some cohorts will transition to the next academic year before the completion of the intervention. For example, the group that is in year 7 when the school is randomised will be in year 8 during the final intervention group run in that school (January–March 2024).

A random selection of eligible adolescents will subsequently be invited to participate in the main study. Parents will receive consent forms detailing the aims of the study, the structure of the intervention and the time commitment expected of participants (see Additional file 1: Appendix), which will also include a consent form. Once parental consent has been obtained, participants will be randomly allocated to one of the three school terms (i.e. the sample will be split into thirds with one third taking part in term 1, a second third taking part in term 2, and the final third taking part in term 3). At the beginning of the allocated term, consent will be sought from the young person, and they will complete the assessment battery comprising of mental health, emotion processing and social relationship measures (see Fig. 4). Participants allocated to the intervention arm of the study will then complete 10 sessions inclusive of individual pre-group sessions, 8 weekly group sessions, and a mid-group session. Participants allocated to the control arm of the study will complete their usual classroom schedule.

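### Adverse events are defined by referral, and only the intervention arm has repeated facilitator contact and CORS cut-offs, so the counts will not be comparable between arms

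*Protocol article*

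**What the plan says.** Ethics and risk management defines the harm outcome by a care decision: "We define an adverse event as an incident that requires referral to a Child and Young Person Mental Health Support Team and/or GP". The preceding sentence sets which events count: "Any adverse events or serious adverse events related to the trial will be stored confidentially by the study team and will be reported" with the main outcomes. The same section says of those delivering the programme: "These clinicians also have up to date training in identifying and referring high-risk participants".

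Under The ReSET group intervention, pupils complete the CORS at the start of every group session. "Clinical cut-offs will be used by facilitators to identify young people who may need additional support during the group". The same sentence extends this to pupils who could be helped by further services, which it does not name. Timing of randomisation gives the intervention arm ten sessions: one individual meeting before the group, eight weekly group sessions and one mid-group meeting. For the other arm it says: "Participants allocated to the control arm of the study will complete their usual classroom schedule".

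Both arms share the baseline, post-intervention and 12-month assessments (Primary impact outcomes; Secondary impact outcomes). Eligibility criteria adds that use of other mental health services is recorded for participants.

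**The concern.** A definition that rests on referral measures two things at once: whether a pupil came to harm, and whether someone was in a position to see it and act. If the second differs by arm, the counts differ by arm even when the first does not. Here it differs by design. A mental health professional meets intervention pupils repeatedly and looks at a wellbeing score against cut-offs. Nothing of that frequency is described for control pupils. The relatedness limit adds to the problem, because few incidents in a pupil's ordinary school day could be called related to a trial in which that pupil receives nothing.

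The counts are to be published with the main results. Under Trial oversight, the advisory committee also acts as data monitoring committee and may recommend halting the project. An excess produced by closer observation could make a harmless programme look harmful. A reader who discounts any excess as closer observation could equally miss real harm. The participants are minors selected for elevated risk.

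**Working it through.** The protocol states no adverse event rate, so there is no figure to reproduce. The check compares the routes by which an event can come to notice, then illustrates what a difference in contact could do.

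**Routes to detection**

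| Route | Intervention | Control |
|---|---|---|
| Baseline and post-intervention assessments | 2 | 2 |
| Group sessions with CORS and cut-offs | 8 | 0 |
| Individual sessions with facilitator | 2 | 0 |
| Trial contacts up to the primary endpoint | 12 | 2 |
| Clinicians trained to identify and refer | at the 10 sessions | none described |
| Research team risk triage, school wellbeing policy | yes | yes |
| Service use recorded | yes | yes |

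Under Adherence, a research team member also audits sessions 1, 2 and 5. Under Data collection plan, assessment measures are completed on a tablet and not under observation, so an assessment may be a weaker chance of detection than a session with a clinician.

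**Illustration 1: detection per contact.** Assumptions: 270 pupils per arm (Sample size calculation), the same true need for referral in both arms, an independent detection chance q at each contact, no detection outside trial contacts, and no relatedness limit.

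Expected events = 270 × need × [1 − (1 − q)^contacts]. At 10% need, 270 × 0.10 = 27.

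| q | Intervention: 27 × [1 − (1 − q)^12] | Control: 27 × [1 − (1 − q)^2] | Ratio |
|---|---|---|---|
| 5% | 27 × 0.460 = 12.4 | 27 × 0.0975 = 2.6 | 4.7 |
| 10% | 27 × 0.718 = 19.4 | 27 × 0.190 = 5.1 | 3.8 |
| 20% | 27 × 0.931 = 25.1 | 27 × 0.360 = 9.7 | 2.6 |

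Need multiplies both columns and cancels from the ratio. Changing it alters the counts only, so it is no test of the ratio.

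**Illustration 2: overall detection, with controls allowed other routes.** Assume 90% of true events are found in the intervention arm and 75%, 50% or 25% in control. The apparent risk ratio is 0.90/0.75 = 1.2, 0.90/0.50 = 1.8 or 0.90/0.25 = 3.6. At an assumed true rate of 5%, expected reports are 12.2 against 10.1, 6.8 or 3.4.

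**Effect of the relatedness limit.** If a fraction a of detected intervention events and a fraction b of detected control events are judged related, each ratio above is multiplied by a/b. If a exceeds b, the imbalance grows. If needs found through the CORS are mostly judged pre-existing, a is small too and both counts may be near zero. The article does not show how relatedness is judged, so neither a nor b can be set.

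**The case against.** Several points on the other side stand.

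- A reader might infer that the CORS is meant to produce referrals, so that the programme manufactures adverse events. The text does not support that. The CORS is described as progress monitoring and as a session tool; its cut-offs flag pupils for support or for unspecified further services; no mental health team or GP trigger is tied to it.
- A reader might infer that the control arm has no route at all. It has some: the shared assessments, triage of urgent concerns that is not confined to one arm, and the school's own policy for pupils in distress. They are less frequent, but they exist.
- A reader might infer that deterioration without referral goes unseen. It does not. SDQ, PHQ-8 and GAD-7 are measured in both arms. Such deterioration is simply not counted as harm.
- The relatedness limit cuts both ways, as the working shows. A pre-existing need noticed through the CORS is not obviously a trial-related event.
- No formal between-arm test of adverse events is stated.
- The adverse event form is in an appendix that is not shown. It may set out collection in both arms.

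These points reduce the certainty and the size of the imbalance. They do not make the counts comparable. The definition and the relatedness limit both stand in the main text, the difference in contact is fixed by the design, and counts published by arm will be compared by readers whether or not a test is planned.

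**Conclusion.** The point holds in a limited form. With a referral-based definition, unequal contact and a relatedness limit, adverse event counts are not comparable between arms. At equal true harm, the likely direction is more recorded events in the intervention arm.

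The size is unknown. The ratios of about 2.6 to 4.7 (12 against 2 contacts, 5-20% detection per contact) and 1.2 to 3.6 (the milder assumptions) rest on assumed detection rates. Illustration 1 treats a tablet assessment and a clinician session as equal chances, which favours a smaller ratio, and gives controls no detection through school, which favours a larger one. Neither illustration applies the relatedness limit.

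Two stronger conclusions go beyond the document: that the counts are certain to be skewed, and that the trial cannot say anything about safety. The first needs event rates and a relatedness procedure that are not given; the second overlooks the symptom measures taken in both arms.

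**What to change.** Base any between-arm comparison of harm on data already collected in the same way in both arms, without a relatedness filter:

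- the proportion whose SDQ Total Difficulties score worsens from baseline by a number of points specified in advance;
- new PHQ-8 or GAD-7 caseness among pupils who were not cases at baseline, using the cut-offs the protocol already intends to apply;
- recorded use of other mental health services, labelled by how the need was first identified. Without that label, this item would carry the same detection imbalance.

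Report referrals first identified by facilitators or through the CORS separately, as an intervention-arm-only count that is not compared with control. Say next to the adverse event table that observation differed between arms.

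The cost is wording in the protocol and analysis plan and a few extra tables. No new visit, instrument or staff is needed. The downside is that the single adverse event count is split in two. Referral practice itself does not change.
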